## Trial design {8}

UPlusE is a prospective, cluster-randomized controlled trial conducted in an outpatient setting. The intervention (screening and, if indicated, consultation by treating doctors) is a new form of healthcare provision. In line with this, UPlusE is being implemented and evaluated within the normal healthcare context. UPlusE is an experimental study within a superiority framework. The effects of the UPlusE intervention will be evaluated by comparing the intervention group with the control group, which receives treatment as usual. If the intervention works as intended, the intervention group will have better values for primary and secondary outcomes. The practices are randomized into an intervention and a control group (1:1 ratio, ensuring an equal distribution of 50% to both groups). The cluster randomization is chosen because the intervention will affect the organizational structure of the entire practice: this includes participant-specific, organizational, and implementation aspects. Thus, counselling parents with mental health/psychosocial issues and encouraging them to utilize the services of mental health practitioners or support services is a responsibility of the entire practice. The cluster randomization ensures that participants in each practice either receive the intervention or serve as the control group, depending on the practice’s assignment. Participants will be recruited nationally from participating paediatric and gynaecological practices. Through screening for depression and psychosocial stress, both groups are expected to yield positive (screened positive) and negative (screened negative) results. In the intervention group, participants receive the intervention as soon as a positive result occurs. Participants in the control group receive treatment as usual. For assessing the success of the intervention (clinical evaluation), comparing participants from both groups with positive results is relevant. Participants in the control group with negative results will additionally be observed concerning the natural course of events from the inclusion point up to U6. The study design is depicted in Fig. 1.

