### Eligibility criteria {10}

#### Inclusion criteria

All pregnant individuals from the 30th week of pregnancy onwards and parents (mothers OR fathers) of children up to 6 months of age (latest entry into the study at the U5-checkup (at child’s age 6 to 7 months) can participate in UPlusE.

Physicians can participate if they are gynaecologists or paediatricians using the practice app. Interventions by gynaecologists or paediatricians will include counselling and motivation of positive screened parents to seek help at support or mental health services. To ensure mental health treatment, a network of mental health specialists is founded, who gave their consent to take part in UPlusE and who will therefore be listed in the app.

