Participants from practices in the intervention group will receive the result of the screening and suitable recommendations for support whenever positively screened during the observation period: pregnant individuals enrolled in gynaecologic practices or parents enrolled in paediatric practices who screen positively during their initial contact with UPlusE will promptly receive the recommendations. Pregnant individuals/parents in the intervention group who are initially screened as negative but are subsequently screened as positive during the course will receive the recommendations from that point onward. As screening tools, the Edinburgh Postnatal Depression Scale (EPDS), the KID-PROTEKT questionnaire, and the scale 1 (impaired bonding) of the Postpartum Bonding Questionnaire (PBQ) will serve. The intervention flow is depicted in Fig. 2. For an EPDS score ≥ 13, trained physicians should encourage the affected parents to promptly consult a mental health practitioner in the region as provided through the app. In case of an EPDS score of 10–12, it is recommended that individuals consider seeking assistance from mental health professionals or, alternatively, ‘Early Prevention’ services. In case of a PBQ scale 1, score ≥ 12, and/or KID-PROTEKT questionnaire ≥ 1 and EPDS < 10, physicians encourage the affected individuals to seek support from ‘Early Prevention’ and other counselling services. The relevant regional addresses will be provided to participants of the intervention group through the apps and the UPlusE website (www.upluse.de). If needed, the physician will support them in making contact. Before each U-checkup, questionnaires are sent again via the app, and the utilization of support services is assessed. The app itself does not guide physicians in treatment recommendations but rather replaces paper questionnaires and calculators to make the screening process more efficient and sustainable.

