### Participant timeline {13}

Depending on entry point (enrolment into the study during pregnancy or at U3-, U4- or U5-checkup) and potential screening point at which a participant in the intervention group screens positive and is motivated for treatment, the duration of the intervention with follow-up observation varies between 6 and 15 months. The intervention is carried out up the U6-checkup (at child’s age 10 to 12 months). The participant timeline is depicted in Fig. 3.

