## Statistical methods

### Statistical methods for primary and secondary outcomes {20a}

The intervention in UPlusE will be scientifically evaluated using a multidimensional approach and various methods (multilevel analyses, process analyses, secondary data analysis) that, in combination, allow for a comprehensive assessment of different aspects of the project.

All data analyses will be conducted using pseudonymized data. After the observation period (U6), the primary and secondary endpoints for parents with psychological and psychosocial issues will be analysed in a group comparison (comparison between the intervention and the control group). Multilevel analyses will be conducted based on the intention-to-treat principle.

Additionally, the trajectory of values and the utilization of services for parents without psychological and psychosocial issues at the time of project inclusion (clinical evaluation) will be descriptively analysed. Quantitative parameters will be analysed using multilevel analyses to correct for cluster randomization. In the case of structural inequality between the intervention and control groups, relevant parameters (such as age, gender, number of pregnancies and births, partnership, socioeconomics—education, occupation, financial situation, severity of depression) will be adjusted for. All tests will be two-tailed with a significance level of alpha = 0.05.

In the analysis, a descriptive evaluation (e.g. symptom severity, child symptoms, service utilization) will be conducted for the group of parents who were positively screened. At the time of U6, a comparison between the intervention and control groups will be performed (e.g. symptom severity, parent–child bonding, child symptoms). Furthermore, across groups, psychosocial stress, depressive symptoms, stigma, and service utilization will be assessed.

The data from the process analysis questionnaires will be analysed descriptively and inferentially.

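### The protocol does not fix which positive screen admits a parent to the primary comparison, and its stated 6-month minimum follow-up does not fit entry at U5

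*Protocol article*

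**What the plan says.** All references are to the protocol article.

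**Who is compared.** Trial design {8} states: "For assessing the success of the intervention (clinical evaluation), comparing participants from both groups with positive results is relevant". It gives no time point for the positive result. The same section says "In the intervention group, participants receive the intervention as soon as a positive result occurs". Intervention description {11a} adds that those "who are initially screened as negative but are subsequently screened as positive during the course will receive the recommendations from that point onward". In the statistical methods {20a}, "the primary and secondary endpoints for parents with psychological and psychosocial issues will be analysed in a group comparison", again without a time point. The next paragraph turns to status at entry: the score trajectories and service use of "parents without psychological and psychosocial issues at the time of project inclusion (clinical evaluation) will be descriptively analysed".

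**Over what period.** The working hypothesis (Objectives {7}) and Table 1 both count utilisation from enrolment or inclusion to the U6 check-up, whenever the first positive screen occurred.

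**How long that is.** Participant timeline {13} says "the duration of the intervention with follow-up observation varies between 6 and 15 months". The inclusion criteria put the "latest entry into the study at the U5-checkup", at a child's age of 6 to 7 months. The abbreviation list puts U6 at 10 to 12 months.

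**The concern.** A parent who is negative at enrolment and positive at U4, say, has no settled place. The Trial design and Intervention description sections point towards including that parent in the comparison of positives. The statistical section points towards a descriptive analysis defined by status at inclusion. Nothing in the article says which governs.

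The choice affects validity. Under {11a}, everyone in the intervention group, screen-negatives included, receives the screening result, information pages and more specific push guidance. Controls receive unspecific information and no results until U6. Any screen after enrolment is therefore taken when the arms have already been handled differently, and being positive on it may depend on allocation. A set built on being positive at any time would compare groups that randomisation no longer makes alike, and applying the intention-to-treat principle within that set would not restore the balance.

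The outcome window adds to the problem. Because utilisation is counted from inclusion, a parent first positive at U6 contributes only time before any feedback on a positive result.

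The length of the window also varies widely with entry point. The outcome is a cumulative yes/no, the sample size uses single rates of 15% and 25% with no time horizon, and the adjustment variables named in {20a} do not include entry point.

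**Working it through.** **1. The plan's base size.** Inputs from Sample size {14}: 15% v 25%, power 0.80; two-sided alpha 0.05 from {20a}. With n per arm and mean rate p̄,

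power = Φ{ [ |p2 − p1|·√n − 1.96·√(2p̄(1 − p̄)) ] / √( p1(1 − p1) + p2(1 − p2) ) }.

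At n = 250 per arm this gives 0.800, so the 500 subjects before clustering and dropout reproduce. The 250 per arm is used below as the effective size.

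**2. Observation windows** (age at U6 minus age at entry; 1 month = 4.35 weeks; birth at week 40):

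| Entry | Shortest | Longest |
|---|---|---|
| Week 30 of pregnancy | 2.3 + 10 = 12.3 months | 2.3 + 12 = 14.3 months |
| U3 (4–5 weeks) | 10 − 1.1 = 8.9 | 12 − 0.9 = 11.1 |
| U4 (3–4 months) | 10 − 4 = 6 | 12 − 3 = 9 |
| U5 (6–7 months) | 10 − 7 = 3 | 12 − 6 = 6 |

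The stated minimum of 6 months is thus the maximum for U5 entrants. With birth at week 42 the longest window is 2.8 + 12 = 14.8 months, so 15 is reasonable rounding.

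**3. If later positives enter the primary set.** Their share is not in the document; one third is assumed. The control rate stays at 15%.

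- Late converters show half the effect: difference = 10 × (2/3 + 1/3 × 1/2) = 8.3 points, so 23.3% v 15%.
- Late converters show no effect: difference = 10 × 2/3 = 6.7 points, so 21.7% v 15%.

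| Late converters | Power, effective n fixed at 250 per arm | Power, set grows to 250 ÷ (2/3) = 375 per arm |
|---|---|---|
| Half effect | 0.66 | 0.83 |
| No effect | 0.49 | 0.66 |

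The right-hand column fits the sample size section better, because its prevalence of 10–15% reads as a single-screen figure. Late converters would then come on top of the planned number.

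**4. Unequal windows.** Assume a constant hazard and equal quarters entering in pregnancy, at U3, U4 and U5, with windows of 13, 10, 7.5 and 4.5 months (mean 8.75). With reference horizon T, the rate over t months is 1 − (1 − p)^(t/T).

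- T = 12: U5 entrants have 1 − 0.85^(4.5/12) = 5.9% v 1 − 0.75^(4.5/12) = 10.2%. The mix averages 11.1% v 18.7%; power 0.67.
- T = 8.75, the mean window: the mix averages 14.9% v 24.6%; power 0.78.

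Neither the entry mix nor the horizon is given in the document.

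**The case against.** The best defence is that this is ambiguity and not an outright contradiction. The Intervention description says who receives recommendations; it does not define an analysis set. The comparison sentence in Trial design names no time point. The descriptive analysis of parents negative at inclusion is introduced as an addition, so it does not strictly exclude anyone from the comparison, and the statistical section can be read as implying a set fixed at inclusion. This stands as far as it goes. It shows that an inclusion-based reading is available, but not that the protocol adopts it. Who is in the primary comparison is something the protocol itself should settle.

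A reader might infer that the contrast is in fact diluted and selected after randomisation. The document does not support that. Both effects arise only if parents first positive after inclusion are analysed in the primary set; with a set fixed at the enrolment screen, neither does.

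A reader might also take the lowest power figures as the expected loss. They rest on an assumed share of late converters and on a fixed set size. If late converters add to the set and show half the effect, power is 83% and nothing is lost. Likewise, that unequal windows pull the rates below 15% and 25% follows only if those are 12-month rates, which the article does not say.

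On entry timing, gynaecological and paediatric practices are randomised by separate procedures, the list of adjustment variables is open-ended, and weighting is foreseen for baseline differences. That weakens any claim that differing entry times must bias the result.

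Two objections to the remedy also stand. Repeated screening is part of the intervention, so restricting to enrolment positives narrows the question. And bonding is screened only in parents, so being positive at enrolment does not mean quite the same for pregnancy entrants.

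**Conclusion.** The point holds in conditional form. The protocol leaves open which positive screen defines the primary comparison, and parents first positive after inclusion could fall in both the comparison and the descriptive group. If they are included, the primary set would be partly selected on screens taken after the arms were treated differently, and would contain parents first positive at U6 in whom feedback can have no effect on the counted outcome.

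The 6-month lower limit is wrong on the document's own ages: U5 entry leaves 3 to 6 months. The upper limit of 15 months needs no change.

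The size of any power loss is not determined by the document. With one third late converters, power is about 49–66% at fixed size, or 66–83% if they add to the set. With an equal entry mix, it is about 67% if 15% and 25% are 12-month rates and 78% if they apply to the average window. These are illustrations of what is at stake, not estimates. The case for settling the definition rests on validity: while two populations remain defensible, the choice between them could be made after the results are seen.

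**What to change.** - **Primary set.** Define it as parents positive on the enrolment questionnaire, completed before any result is released, with utilisation counted from that date to U6.
- **Later positives.** Report parents first positive after enrolment as a separate secondary group, counted from their first positive screen.
- **Entry point.** Include it (pregnancy, U3, U4, U5) in the primary model, because windows run from about 3 to 14–15 months. This also absorbs part of the difference in what is screened at each entry point. The exact model form can be left to the analysis plan.
- **Timeline.** Correct the stated range in Participant timeline {13} to about 3 to 15 months.

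The cost is wording in the protocol and analysis plan; all the data are already to be collected. The planned size need not change on this account, since it reads as based on a single-screen prevalence. The real price is that late converters leave the primary comparison, so the benefit of repeated screening for them is shown only in a secondary analysis. The change should be recorded before outcomes are compared by arm. It does not address participants being enrolled after open practice allocation, which is a separate matter.

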**Fig. 1 Fig1:**
[figure not shown]
UPlusE design

## Methods: participants, interventions, and outcomes

### Study setting {9}

UPlusE is a new module of an already established healthcare program (BKK Starke Kids) which offers health and preventive services for children and adolescents beyond regular healthcare to their customers. The UPlusE-module addresses the parents’ mental health and psycho-social distress. UPlusE will also be open to insured individuals from other insurers.

Outpatient gynaecologists and paediatricians throughout Germany will be recruited to participate in UPlusE with their practices. One requirement for the physicians to participate in UPlusE is the utilization of the practice apps “My Gynaecology Practice” (German: "Meine GynPraxis”) or “My Paediatric Practice” (German: "Meine pädiatrische Praxis”) in their practices. The apps are well-established communication tools connecting patients with their gynaecologists respectively parents with their paediatrists. Participating physicians will receive a certified Continuing Medical Education (CME) online training free of charge, focusing on managing the screening process and the management of peripartum mental health disorders.

### Eligibility criteria {10}

#### Inclusion criteria

All pregnant individuals from the 30th week of pregnancy onwards and parents (mothers OR fathers) of children up to 6 months of age (latest entry into the study at the U5-checkup (at child’s age 6 to 7 months) can participate in UPlusE.

Physicians can participate if they are gynaecologists or paediatricians using the practice app. Interventions by gynaecologists or paediatricians will include counselling and motivation of positive screened parents to seek help at support or mental health services. To ensure mental health treatment, a network of mental health specialists is founded, who gave their consent to take part in UPlusE and who will therefore be listed in the app.

#### Exclusion criteria

Exclusion criteria include lack of capacity to give consent or an inability to complete the questionnaires in the app (no smartphone, insufficient language, or reading skills). This study thus excludes individuals who cannot operate a smartphone and those who do not speak sufficient German. Many people who do not yet have a sufficient command of the German language use translation programs on their smartphones. If pregnant individuals/parents understand the informed consent and questionnaires adequately with the help of translation programs, they can naturally be included.

### Who will take informed consent? {26a}

UPlusE participants are required to install one of the aforementioned apps on their smartphones in order to take part. Pregnant individuals will be recruited and enrolled by participating gynaecologists, and parents will be recruited and enrolled by paediatricians. Enrolment is achieved through a digital signing of the consent form and data protection declaration within the practice apps. A comprehensive patient information document precedes the consent form. The consent forms are then digitally transmitted to the project management for documentation and compliance with retention obligations.

### Additional consent provisions for collection and use of participant data and biological specimens {26b}

In UPlusE, data is collected through questionnaires. Additionally, health insurance data from the participating health insurance company (58 BKKs) will be used to descriptively analyse the utilization of health system services and their costs. Detailed information about these data collection processes is provided in the patient information. The informed consent form, in which participants agree to participate, refers to this data collection. No other data is collected, and no biological samples or similar materials are taken.

## Interventions

### Explanation for the choice of comparators {6b}

Up to the final data collection point at U6, participants in the control group will receive regular healthcare (treatment as usual). This group will serve as the comparator for the intervention. At the conclusion of the study, they will be provided with the benefits of the intervention (feedback to the screening results and, if necessary, recommendations for further treatment).

### Intervention description {11a}

The intervention is delivered to participants through the practice apps. These apps are established communication tools used for conveying practice information and communication, scheduling, or reminding appointments.

With the UPlusE module, the following interventions are being conducted:All participants receive information/guidance about childbirth and parent–child interaction through automatically sent push notifications. The intervention group gets more specific guidance; the control group gets unspecific information.All participants are screened regularly for depression, psychosocial stress, and impaired bonding (in parents) through questionnaires.All participants in the intervention group receive their screening result, subsequent information about peripartum depression, psychosocial distress, distress with their babies, and recommendations for treatment and/or counselling on special pages of the website www.upluse.de.Participants in the intervention group with a positive screening result receive their screening result with subsequent recommendations for treatment and/or counselling from their treating physician. Simultaneously, regional contact information for mental health practitioners, “Early Prevention” and counselling services, peers, and support groups are made available in the apps’ data pool.

Participants from practices in the intervention group will receive the result of the screening and suitable recommendations for support whenever positively screened during the observation period: pregnant individuals enrolled in gynaecologic practices or parents enrolled in paediatric practices who screen positively during their initial contact with UPlusE will promptly receive the recommendations. Pregnant individuals/parents in the intervention group who are initially screened as negative but are subsequently screened as positive during the course will receive the recommendations from that point onward. As screening tools, the Edinburgh Postnatal Depression Scale (EPDS), the KID-PROTEKT questionnaire, and the scale 1 (impaired bonding) of the Postpartum Bonding Questionnaire (PBQ) will serve. The intervention flow is depicted in Fig. 2. For an EPDS score ≥ 13, trained physicians should encourage the affected parents to promptly consult a mental health practitioner in the region as provided through the app. In case of an EPDS score of 10–12, it is recommended that individuals consider seeking assistance from mental health professionals or, alternatively, ‘Early Prevention’ services. In case of a PBQ scale 1, score ≥ 12, and/or KID-PROTEKT questionnaire ≥ 1 and EPDS < 10, physicians encourage the affected individuals to seek support from ‘Early Prevention’ and other counselling services. The relevant regional addresses will be provided to participants of the intervention group through the apps and the UPlusE website (www.upluse.de). If needed, the physician will support them in making contact. Before each U-checkup, questionnaires are sent again via the app, and the utilization of support services is assessed. The app itself does not guide physicians in treatment recommendations but rather replaces paper questionnaires and calculators to make the screening process more efficient and sustainable.

